### 9.2 Subject Safety Information

A list of risks is presented to the subject in the consent form, along with contact information to reach an investigator in case of a perceived adverse event or side effect. Subjects are given a copy of the consent form and instructed to keep this for the duration of the study.

### 9.3 Availability of the Investigator

[name], the Principal Investigator, or her designee is available 24 hours a day, seven days a week for study-related questions at both Tufts Medical Center and Massachusetts General Hospital. In the event that she is not available by cell phone or pager, her pager number will be forwarded to another investigator who will be familiar with the study protocol and has [name] contact information.

### 9.4 Adverse Events

#### 9.4.1 Definitions

An **adverse event (AE)** is any undesirable experience associated with the use of a medical product in a subject (<http://www.fda.gov/medWatch/report/DESK/advevnt.htm>). An AE can therefore be any

unfavorable and unintended sign (including an abnormal laboratory finding), symptom, or disease temporally associated with the use of a study drug. Study subjects will be monitored for the occurrence of events from the day of enrollment for a maximum period of 2 months, although intense monitoring of adverse events will occur during the first 28 days when the subject is taking LGG. The occurrence of an AE may come to the attention of study staff during study visits and interviews with a study subject presenting for medical care, or upon review by a study monitor. In addition, subjects will be evaluated in person or by telephone and asked about unanticipated adverse events. We will use both open-ended questions and specific questions about possible adverse effects, such as presence of diarrhea and other abdominal symptoms.

#### **9.4.2 Recording of Adverse Events**

Each adverse event will be recorded on an Adverse Event Case Report Form which will include the following information:

- Description of symptoms and/or event
- Onset and Duration, including intermittent or not
- Adverse Event Severity (including determination if the event qualifies as a Serious Adverse Event – see Section 9.4.2.1 below)
- Assessment of relationship between the study drug and adverse event (see Section 9.4.2.2 below)
- Action(s) taken to treat the adverse event
- Outcome

Once identified, all AEs (including serious) will be followed until resolved or until the PI considers that the subject is stable. Evaluation of AEs will be done during follow-up visits, as well as during unscheduled visits, and scheduled telephone calls. All communications, examinations, and testing that occurs as a result of the AE will be clearly documented on AE forms and the appropriate CRFs. Changes in the severity of an AE will be documented to allow an assessment of the duration of the event at each level of intensity to be performed.

If events occur which raise questions about the safety of continued administration of LGG, the subject's physician will have the option to withdraw the subject from the study.

##### **9.4.2.1 Adverse Event Severity**

All AEs will be assessed by the clinician and classified according to the **FDA's Guidance for Industry: Toxicity Grading Scale for Healthy Adult and Adolescent Volunteers Enrolled in Preventive Vaccine Clinical Trials** as recommended by FDA. See Appendix A. As per the FDA's recommendation, we will use the following grading scale to classify adverse events:

- Mild (Grade 1): an event which requires no treatment and does not interfere with the subject's daily activities.
- Moderate (Grade 2): an event which may cause some interference with the subject's daily activity but does not require medical intervention
- Severe (Grade 3): an event which prevents usual daily activity (incapacitating; unable to perform usual activities; requires bed rest or absenteeism) and requires medical intervention.
- Potentially life threatening (Grade 4): an event which results in an ER visit or hospitalization

A **serious adverse event (SAE)** is defined as an AE that meets one of the following conditions (<http://www.fda.gov/medWatch/report/DESK/advevnt.htm>)

- Death – Report if the subject's death is suspected as being a direct outcome of the adverse event
- Life-Threatening – Report if the subject was at substantial risk of dying at the time of the adverse event or it is suspected that the use or continued use of the product would result in the subject's death.
- Hospitalization (initial or prolonged) – Report of admission to the hospital or prolongation of a hospital stay results because of the adverse event.
- Disability – Report if the adverse event resulted in a significant, persistent, or permanent change, impairment, damage or disruption in the subject's body function/structure, physical activities or quality of life.
- Congenital Anomaly – Report if there are suspicions that exposure to a medical product prior to conception or during pregnancy resulted in an adverse outcome in the child.
- Requires Intervention to Prevent Permanent Impairment or Damage – Report if you suspect that the use of a medical product may result in a condition which required medical or surgical intervention to preclude permanent impairment or damage to a subject.

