## 9.5 Withdrawal of Subjects

The study drug will be discontinued and the subject withdrawn from the study if any of the following occur:

- An adverse event, intercurrent illness, or other medical condition or situation occurs such that continued participation in the study would not be in the best interest of the subject
- If an enrolled subject begins immunosuppressive medication or events occur which raise questions as to the safety of continued administration of LGG, and/or the subject's primary care physician wishes to withdraw the subject from the study
- Grade 3 or Grade 4 gastrointestinal side effects
- *Lactobacillus* bacteremia or invasive *Lactobacillus* infection
- Subject withdraws consent
- Subject is lost to follow-up

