|---------------------------|----------------------------------------------------------|------------------------------------------------------------------------------------------|----------------------------------------------------------------------------------|---------------------------------------------------|
| Nausea/vomiting           | No interference with activity or 1 – 2 episodes/24 hours | Some interference with activity or > 2 episodes/24 hours                                 | Prevents daily activity, requires outpatient IV hydration                        | ER visit or hospitalization for hypotensive shock |
| Diarrhea                  | 2 – 3 loose stools or < 400 gms/24 hours                 | 4 – 5 stools or 400 – 800 gms/24 hours                                                   | 6 or more watery stools or > 800gms/24 hours or requires outpatient IV hydration | ER visit or hospitalization                       |
| Headache                  | No interference with activity                            | Repeated use of non-narcotic pain reliever > 24 hours or some interference with activity | Significant; any use of narcotic pain reliever or prevents daily activity        | ER visit or hospitalization                       |
| Fatigue                   | No interference with activity                            | Some interference with activity                                                          | Significant; prevents daily activity                                             | ER visit or hospitalization                       |
| Myalgia                   | No interference with activity                            | Some interference with activity                                                          | Significant; prevents daily activity                                             | ER visit or hospitalization                       |

| Systemic Illness                                                            | Mild (Grade 1)         | Moderate (Grade 2)                                          | Severe (Grade 3)                                   | Potentially Life Threatening (Grade 4) |
|------------------------------------------------------------------------------------|-------------------------------|--------------------------------------------------------------------|-----------------------------------------------------------|-----------------------------------------------|

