## APPENDIX C: SYMPTOM DIARY

### SYMPTOM DIARY

**Instruction:** Please check the box if YES for each symptom you have had each day. Please rate the symptom when it was bothering you the most as:

**Mild** - symptoms do not interfere with your daily activities, no medical therapy required.

**Moderate** - symptoms which may interfere with your daily activities, no or minimal medical therapy required

**Severe** - symptoms which interrupt your daily activities, medical therapy required, hospitalization possible

**Very severe** - symptoms which cause extreme limitations in your daily activity that required medical therapy and hospitalization

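### Adverse events are graded on two unreconciled scales, so the same diarrhea can differ by two grades in either direction; separately, the diary and telephone form require no stool or vomiting counts.

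*Protocol*

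**What the plan says.** **Primary outcome.** Protocol Section 3.2.1 counts new Grade II-IV toxicities on the FDA scale that are possibly or probably related to LGG.

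**Grading.** Section 9.4.2.1 begins "All AEs will be assessed by the clinician and classified according to the" FDA guidance, with a pointer to Appendix A. It presents what follows as the FDA's recommendation and adds "we will use the following grading scale to classify adverse events". That list rests on interference with activity and need for treatment. Grade 1 is "an event which requires no treatment and does not interfere with" daily activities. Grade 3 is "an event which prevents usual daily activity (incapacitating; unable to perform usual activities; requires bed rest or absenteeism) and requires medical intervention".

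**Appendix A, Systemic (General) table.** Diarrhea is Grade 1 at 2-3 loose stools, Grade 2 at 4-5 stools, and Grade 3 at "6 or more watery stools or > 800gms/24 hours or requires outpatient IV hydration". Weight bands stand alongside the counts, and Grades 1-3 carry no activity criterion. Vomiting more than twice in 24 hours is Grade 2 even without interference.

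**Thresholds.** Section 9.4.3 requires new Grade 3 or 4 toxicities to be reported to the IRBs and the DSMB chair within 72 hours. Section 9.5 withdraws a subject for "Grade 3 or Grade 4 gastrointestinal side effects".

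**Data capture.** The Appendix C diary has a daily tick and a severity rating for each symptom, with no count field. Its Severe category reads "symptoms which interrupt your daily activities, medical therapy required, hospitalization possible". The telephone form (Section 7.2, calls on Days 3, 7 and 14) is to ask the diary's questions, with open-ended questions added. Under Section 9.1 a study physician follows up symptoms reported on a scheduled call and rates them.

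**The concern.** Safety and tolerability is the only primary objective, and Section 9.4.1 singles out diarrhea and other abdominal symptoms for specific questioning. For these events the protocol gives a clinician two sets of criteria and no rule for choosing between them. Someone who follows the list printed in Section 9.4.2.1 can reach a grade that contradicts the scale named in the primary outcome. Two physicians at the two sites could grade identical episodes differently, and both could point to the protocol. The grade decides whether an event can count in the primary outcome, whether it is reported within 72 hours, and whether a gastrointestinal event ends treatment.

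A second, independent gap lies in what is collected. Appendix A needs counts for diarrhea and vomiting, and no form shown in the protocol asks for them. Counts that were never recorded cannot be recovered at analysis.

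**Working it through.** The protocol gives no figure to reproduce: Section 11.1 states that the sample size does not come from a power analysis. The check applies both sets of criteria to the same events and then sizes the effect of one reclassification.

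**Step 1: grade the same event twice.** Assumptions: no ER visit or admission, stool weight within the band that matches the count, no outpatient IV hydration, and treatment read as equivalent to medical intervention.

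| Event in 24 hours | Section 9.4.2.1 list | Appendix A row | Thresholds crossed |
|---|---|---|---|
| At least 6 watery stools, untreated, no interference | 1 | 3 | Primary outcome, 72-hour report, GI withdrawal |
| 5 stools, untreated, no interference | 1 | 2 | Primary outcome |
| 3 loose stools, some interference, untreated | 2 | 1 | Primary outcome |
| 3 loose stools, prevents activity, needs non-IV intervention | 3 | 1 | All three |
| 3 vomiting episodes, untreated, no interference | 1 | 2 | Primary outcome |

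The largest gap is two grades, and it occurs in both directions. For vomiting, the Appendix A count separates only Grades 1 and 2. The Section 9.4.2.1 list also leaves some events without a grade, such as one that is treated but does not interfere, or one that prevents activity but is untreated.

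**Step 2: effect on the primary proportion.** One reclassified subject changes the proportion by 1/n: 1/15 = 6.7 points and 1/10 = 10 points. Exact (Clopper-Pearson) 95% intervals, computed here to show scale because the plan is descriptive, have an upper limit of 1 − 0.025^(1/n) when no events occur:

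- n = 10: 0/10 gives 0 to 30.8%; 1/10 gives 0.3 to 44.5%.
- n = 15: 0/15 gives 0 to 21.8%; 1/15 gives 0.2 to 31.9%.

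**Step 3: can the counts be obtained?** The diary and the questions repeated from it yield a tick and a rating. A physician can ask for a count after a scheduled call, but the last such call is nominally on Day 14. A count from Days 15 to 28 would then rest on up to 14 days' recall at the Day 28 visit, and one from Days 29 to 56 on up to 28 days' recall at Day 56, unless the subject calls.

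**Step 4: compare the diary wording.** Diary Moderate allows minimal medical therapy, while Section 9.4.2.1 Grade 2 excludes medical intervention. Diary Severe admits possible hospitalization, while Section 9.4.2.1 places hospitalization at Grade 4. Appendix A's diarrhea row uses counts or weight for Grades 1-3. The diary is therefore a third wording.

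**The case against.** The strongest reply is that the scale is already settled. Section 3.2.1 names the FDA guidance, Section 9.4.2.1 opens with it, and the functional list closely tracks Appendix A's own general row for illness or clinical adverse events. On that reading it is the residual row restated. This is plausible and favours Appendix A for the primary outcome. But Section 9.4.2.1 does not confine the list to events without their own row, and it offers the list as the FDA's recommendation, so the conflict remains as written.

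It can also be said that six watery stools with no interference is a corner case, that counting in the primary outcome further needs a relatedness judgement, that the analysis is descriptive, and that the DSMB receives all Grade 1-4 toxicities. These points limit the consequence. They do not remove it, since milder and more ordinary combinations in the table still cross the Grade II line.

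Four stronger readings are tempting and not supported:

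- *That Appendix A grades cannot be derived between visits.* The clinician does the grading and may ask for counts, the adverse event form takes a description, and the visit questionnaires are not shown. The gap is that nothing shown requires a count.
- *That the missing counts cause the Grade 1 versus Grade 3 split.* The split comes from the two scales alone.
- *That the functional scale under-grades.* The protocol offers no evidence of a direction, and the table shows differences both ways.
- *That the choice of scale, or the diary's wording about ER visits, moves diarrhea in or out of Grade 4.* Both scales put an ER visit or hospitalization for diarrhea at Grade 4, and a subject's diary rating is not the clinician's grade. The suspension rule in Section 9.7 also requires a probable or definite relationship.

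**Conclusion.** The point holds as an inconsistency in how adverse events are graded, with a separate weakness in data capture. The protocol supports two different grades for the same gastrointestinal event, up to two grades apart and in either direction, across three operative thresholds. The primary proportion shifts by 6.7 to 10 points per reclassified subject, provided the event is new and judged possibly or probably related. How often this would happen cannot be estimated from the protocol, and no bias in one direction is claimed. The conclusion rests on reading the Section 9.4.2.1 list as applying to adverse events generally, which is what its text says. It should be corrected, because grade definitions and diary content are fixed in the protocol.

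**What to change.** 1. Reconcile Section 9.4.2.1, Appendix A and Appendix C so that one stated grading rule applies, with explicit precedence between symptom-specific rows and the functional list. It should be consistent with the FDA scale that Section 3.2.1 already names for the primary outcome. Which grade governs withdrawal and suspension is a clinical decision for the sponsor and is not proposed here.
2. Add two daily numbers to the diary and the telephone form: loose stools in 24 hours and vomiting episodes in 24 hours.
3. Align the diary's severity wording with the reconciled grades.

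The cost is a revised diary and telephone form, an IRB notification, and a slightly longer daily entry for subjects.

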#### 9.4.2.2 Assessing the Relationship between Study Drug and Adverse Event

The principal investigator will classify the relationship of the study protocol to the adverse event as follows:

- Not related: The event is clearly related to factors such as the subject's clinical state, not to therapeutic interventions associated with the study protocol.
- Remote: The event was most likely related to factors such as the subject's clinical state, not to therapeutic interventions associated with the study protocol.
- Possible: The event follows a reasonable temporal sequence from consuming LGG, but is possibly related to factors such as the subject's clinical state.

- **Probable:** The event follows a reasonable temporal sequence from consuming LGG and cannot be reasonably explained by factors such as the subject's clinical state.
- **Highly Probable:** The event follows a reasonable temporal sequence from consuming LGG, and cannot be reasonably explained by factors such as the subject's clinical state. In addition, the event occurs immediately following ingestion or application of study drug or reappears on repeat exposure, if the PI considers it safe to re-expose the subject to study drug.

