### 3.2 Outcome Measures

#### 3.2.1 Primary Outcome Measure

Occurrence of adverse events defined as a new Grade II-IV toxicity (FDA's Guidance for Industry: Toxicity Grading Scale for Healthy Adult and Adolescent Subjects Enrolled in Preventative Vaccine Clinical Trials, September 2007), that are possibly or probably related to administration of LGG. Adverse events will be detected during study visits with standardized questionnaires, medical history, vital signs, physical examinations, laboratory tests and review of subject diaries as well as between study visits on telephone calls based on responses to adverse event questionnaires.

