## 4 STUDY DESIGN

This is a phase I, open label clinical trial to evaluate the safety of *Lactobacillus rhamnosus* GG (LGG), ATCC 53103 in 10-15 elderly subjects. Enrollment of subjects is estimated to take approximately 3 months. Subject participation is approximately 3 months. The study will be conducted in elderly subjects at the Clinical Research Centers (CRC) at Tufts Medical Center and Massachusetts General Hospital. Subjects will be seen as outpatients. The study drug dose is  $2 \times 10^{10}$  LGG per day ( $1 \times 10^{10}$  LGG per capsule, 2 capsules per day). The study drug will be given orally twice a day for 28 days. The first dose will be ingested under observation in the CRC. Subjects will be evaluated during study visits at screening, Day 0 (baseline), Day 28 (+/- 2 days), and Day 56 (+/- 1 week), as well as on telephone calls on Days 3 (+/- 1 day), 7 (+/- 2 days), 14 (+/- 2 days).

Grade 2 or higher adverse events that were not present at baseline will be assessed using standardized questions asked during each study visit and telephone call, standardized physical examinations, and the results of laboratory tests. Subject diaries will be reviewed at each visit. Subjects will be reminded during the course of the study to contact the PI if any issue arises. Clinical laboratory tests will be performed at the CLIA-approved clinical laboratories at Tufts Medical Center and the Massachusetts General Hospital. Cultures of the stool and LGG capsules will be performed in [name] research laboratory at Tufts Medical Center to assess for the presence of LGG. Bacterial DNA from nasopharyngeal and stool specimens will be processed in the CRC research laboratory for microbiota analysis.

A Data and Safety Monitoring Board (DSMB), see Section 9.7, will oversee the study. The DSMB will review the safety data approximately every six months. There will be no formal interim analysis. The DSMB will report on whether or not to continue the study after each review. The report will contain the following information regarding the study's safety to date:

- Overview of study status
- Summary of safety data for each subject through day 56
- Summary safety assessment

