### **11.3 Statistical Analysis**

#### **11.3.1 Safety**

Adverse events reported by subjects who receive at least one dose of the study will be summarized by body system and relationship to study product. The rate of Grade II or higher vital signs, physical examinations and laboratory tests will be calculated and summarized using descriptive statistics. Concomitant medications and significant non-drug therapies will also be reported. The precise type of missing data, should it occur, will be described.

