### **15.1 Data Management Responsibilities**

All source documents and laboratory reports must be reviewed by the clinical team and data entry staff, who will ensure that they are accurate and complete. Adverse events must be graded, assessed for severity and causality, and reviewed by the PI or designee.

Data collection is the responsibility of the clinical trial staff under the supervision of the PI. During the study, the investigator must maintain complete and accurate documentation for the study.

[name] group will assume responsibilities for data management and quality review, and [name] will perform the statistical analysis and report the study data.

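### For events that fit both Remote and Possible, the primary safety count rests on the investigator's judgment; report the all-cause Grade II-IV count beside it

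*Protocol*

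**What the plan says.** - **Outcome.** Section 3.2.1 has a single primary outcome: new Grade II-IV toxicities "that are possibly or probably related to administration of LGG".
- **Rater.** Section 9.4.2.2: "The principal investigator will classify the relationship of the study protocol to the adverse event as follows". Section 15.1 words it a little differently: "Adverse events must be graded, assessed for severity and causality, and reviewed by the PI or designee".
- **Design.** Section 4: "This is a phase I, open label clinical trial to evaluate the safety of" LGG. One treatment is given to 10-15 subjects, and no control arm is described.
- **Scale.** Section 9.4.2.2 has five categories: *Not related*, *Remote*, *Possible*, *Probable* and *Highly Probable*. *Remote* reads "The event was most likely related to factors such as the subject's clinical state, not to therapeutic interventions associated with the study protocol". The next step up reads "Possible: The event follows a reasonable temporal sequence from consuming LGG, but is possibly related to factors such as the subject's clinical state".
- **Analysis.** Under Section 11.3.1, adverse events in dosed subjects are "summarized by body system and relationship to study product". The same section calls for a Grade II or higher rate for vital signs, physical examinations and laboratory tests, with no condition on relatedness.
- **Oversight.** Under Section 9.7 the DSMB receives all Grade 1-4 toxicities, and is asked to review the relatedness assessment for Grade 4 events and SAEs.

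**The concern.** Safety and tolerability are the trial's only primary objective. Because Section 3.2.1 builds relatedness into the outcome, the line between counted and not counted falls between *Possible* and *Remote*. If the two definitions overlap, the same event can be counted or left out without breaching the protocol. The rater knows the treatment, and no comparator shows how often such events occur without LGG. With 10-15 subjects, one or two ratings are a large share of the result.

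A second mismatch sits beside this one. Section 3.2.1 names two levels of relatedness, while the scale has a third and stronger one, *Highly Probable*. Read literally, the outcome leaves out the events most firmly attributed to LGG.

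**Working it through.** There is no design figure to reproduce. Section 11.1 says the sample size does not come from a power analysis, and no expected event rate or threshold is attached to the primary outcome. The check is therefore a reading of the definitions, followed by exact intervals for illustrative counts.

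**Step 1: do the categories overlap?**

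| Category | Timing condition | Role of clinical state | Counted under 3.2.1? |
|---|---|---|---|
| Remote | none | most likely the cause | no |
| Possible | reasonable sequence after LGG | possibly the cause | yes |
| Probable | reasonable sequence after LGG | cannot reasonably explain the event | yes |
| Highly Probable | as Probable, plus immediate onset or recurrence on re-exposure | cannot reasonably explain the event | not named |

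Take an event that follows LGG in reasonable sequence and is most likely due to the subject's clinical state. It meets *Remote*, which has no timing condition. It also meets *Possible*, because something most likely due to clinical state is also possibly due to it. No rule says which prevails. *Probable* and *Highly Probable* contradict *Remote* on clinical state, so events at those levels are outside the overlap.

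**Step 2: size.** Let k be the number of subjects whose only new Grade II-IV events lie in the overlap, and suppose no other subject has a counted event. The primary count can then be any number from 0 to k. The exact (Clopper-Pearson) 95% limits for x of n are:

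- lower: the 0.025 quantile of Beta(x, n - x + 1), or 0 when x = 0;
- upper: the 0.975 quantile of Beta(x + 1, n - x), which for x = 0 is 1 - 0.025^(1/n).

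For x = 0 the upper limits are 1 - 0.025^(1/10) = 30.8% and 1 - 0.025^(1/15) = 21.8%. With k = 2 (an assumption):

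| Rating of the two subjects' events | n = 10 | n = 15 |
|---|---|---|
| both Possible | 2/10 = 20% (2.5-55.6%) | 2/15 = 13.3% (1.7-40.5%) |
| one of each | 1/10 = 10% (0.3-44.5%) | 1/15 = 6.7% (0.2-31.9%) |
| both Remote | 0/10 = 0% (0-30.8%) | 0/15 = 0% (0-21.8%) |

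With k = 3 the all-*Possible* result is 3/10 = 30% (6.7-65.2%) or 3/15 = 20% (4.3-48.1%), against the same zeros.

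**Step 3: the all-cause count.** If subjects are counted regardless of relationship, the result is k/n in every row, because the rating no longer enters.

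**Step 4: what the existing summaries recover.** The unfiltered Grade II or higher rate in Section 11.3.1 covers vital signs, examinations and laboratory tests. The symptoms in the Appendix C diary, mostly gastrointestinal, fall under the adverse event summary, whose stated dimensions are body system and relationship. Grade is not one of them.

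**The case against.** The case on the other side has several parts.

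- **The scale is ordinal.** *Most likely* against *possibly* reads as a ranking of likelihood, and a consistent rater could use it that way. This is probably the intention, but the text does not state it. Nor is the timing condition met automatically: follow-up runs to Day 56, four weeks after dosing ends. The overlap matters most during the 28 days of twice-daily dosing.
- **Excluded events do not disappear.** This stands. Severity and relationship are recorded for each event (Section 9.4.2), events are summarised by relationship, the DSMB receives all grades, and it reviews relatedness for Grade 4 events and SAEs. That review does not extend to Grade 2 events or non-serious Grade 3 events.
- **Table layout belongs to the SAP.** Fair as to layout, and the SAP is not at hand. The outcome definition and the scale, however, are fixed in the protocol.
- **An all-cause rate has its own weakness.** Without a comparator it cannot separate drug effect from background. This stands, and it is why the two counts belong together. A related-event outcome is defensible in a small Phase I study.

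A reader might infer more than the documents support:

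- *The safety result can be taken to zero by judgment alone.* Not if any event is *Probable*, since such an event cannot be rated *Remote*.
- *The filtered rate cannot be compared with Stages II and III.* Section 2.1.10 only outlines those stages and does not say how their adverse events will be analysed. They also add a vaccine, which limits comparison under either definition.
- *The pilot shows that many events will need this rating.* Its 14/21 (67%) on LGG and 17/21 (81%) on placebo are events of any grade in adults aged 18-49 given LAIV. They show only that background events can be common.

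**Conclusion.** The point holds within limits. The only primary outcome depends on a relatedness rating made by the principal investigator in an open-label, uncontrolled study, and the two categories on either side of the counting line are not mutually exclusive. For events in that overlap the count is a matter of judgment. In the two-subject illustration this is a difference of 20 percentage points at n = 10 and 13.3 at n = 15.

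Those sizes assume that two subjects have only overlap events and that nobody has a *Probable* event. The protocol predicts neither. No test, threshold or go/no-go rule is tied to the primary rate, so the consequence lies in how the safety result reads. The documents do not show that harm would be hidden, and they do not require the related-event outcome to be dropped. They do support an inexpensive improvement: an all-cause count beside the related one, and a scale that matches the outcome.

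**What to change.** 1. In Sections 3.2.1 and 11.3.1, report the number of subjects with one or more new Grade II-IV toxicities after the first dose, regardless of relationship and with symptoms included. Place the investigator-rated related subset directly beneath it.
2. In Section 9.4.2.2, make *Remote* and *Possible* mutually exclusive, for example by stating which prevails when timing is reasonable and clinical state is the most likely cause.
3. Reconcile the wording of Section 3.2.1 with the scale, and state whether *Highly Probable* events count. Section 9.7 also uses a level, definitely related, that is absent from the scale, so those terms should be aligned too.

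The cost is a few sentences. Section 4 already provides for assessing Grade 2 or higher events not present at baseline, and the case report form captures grade and relationship, so no new data or independent assessor is needed. The downside is that the all-cause count includes background events and will look less favourable.
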